## **Sample size and justification**

We are anticipating at least 60 individuals in each study arm at the closure of the study.

A recent systematic review of 44 high-quality exercise trials for knee OA pain (3537 participants) (106) found an average effect of 12/100 VAS points corresponding to 0.49 standard deviations. A sample size of n=60 per group is necessary to achieve 75% stat power. The estimated dropout rate for exercise interventions is 12%, therefore, a sample of 67 per arm will be recruited to achieve at least 75% power.

## **ADVERSE EVENTS**

Increase in the knee, hip or back pain are possible adverse effects (106). One case of raised hypertension has been reported by a previous study (111).

Participants will be asked to contact the study site immediately in the event of any serious adverse event. Any adverse event will be recorded and closely monitored until resolution, stabilisation or until it has been shown that the study treatment / intervention is not the cause. Participants can contact physiotherapists (SG) if there is any adverse event. The CI shall be informed immediately of any serious adverse events and shall determine seriousness and causality in conjunction with any treating medical practitioners.

Any serious adverse event (s) related to this study will be recorded and reported to the REC as part of annual reports. Unexpected serious adverse events will be reported within timeframes to the REC and CI will be responsible for all adverse event reporting.

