## **Known Side Effects**

Increased knee, hip or low back pain and one reported case of increased hypertension (106).

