## **Study Regimen**

Participants seeking care for osteoarthritis will be informed of the study both orally and in writing. Those who qualify for the study will sign the informed consent and the participants will be randomised to interventional group and control group. The exception applies to those Participants who have not had knee X-rays in last 12 months. These individuals will be called to the hospital. After gaining a valid consent, knee radiographs will be taken, and their X-rays will be verified by experienced staff. Once, a definite eligibility criterion (K/L score at least 1 or above) is established in such cases, the potential participants will be randomised to interventional group and control group like the other individuals. Blinding such interventional studies are difficult to achieve as participants will establish as to in which group they are in however study will be blinded to the examining clinician. Controlled and interventional groups individuals will be recruited for this study. Interventional groups will have an assessment session with the experienced staff and NRS, QST, WOMAC, MSK-HQ, 30CST, TUG, PSQI, MSK-USS, urine and blood samples will be taken at baseline.

Interventional group will shortly after that receive a link via email, which will be used to log-in to Joint Academy online portal. After log-in has been achieved, the intervention starts. It consist of a 6-week internet-based physical therapy program that provides information, exercises, contact details of a personal physiotherapist, education about lifestyle and behavioural changes. This intervention can be accessed using a smartphone, a tablet or a computer. The program encourages the physical activity by sending email prompts on a regular basis to help participants to continue during the whole treatment. Initially, participants will answer an online-questionnaire covering areas such as joint pain intensity, health-related quality of life, physical function as well as being instructed in and performing a physical test assessing lower limb strength / physical function. This questionnaire will form a part of online baseline assessment. Exercises itself consistent of knee and hip exercises along with some functional activities such as sit to stand and stairs climbing. Interventional group will be given actigraphy device (a device to monitor sleeping pattern) which is CE marked. Therefore, their sleeping pattern can be recorded quantitatively.

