Once exercises programme is finished in six weeks, the participants will fill in the same questionnaire and perform the physical tests, to enable evaluation. There are two face-to-face meetings between participants and physiotherapist/nurse, at enrolment and after six weeks. The physiotherapist is also available via asynchronous online chat or over the phone during the 6-week study period. After six weeks, participants can continue with sustain-program for self-management, mainly focusing on the continuation of treatment, performing the exercises regularly.

Control group will continue with their routine self-management which is offered in the community setup. They will be assessed on NRS, QST, WOMAC, MSK-HQ, PSQI, 30CST, TUG, isokinetic muscles strengthen of quadriceps, urine and blood samples at baseline. Control group will also get the actigraphy to monitor sleeping pattern of that group. They will be re-assessed after six weeks on the primary objective measures to see if they have made any difference by following self-management strategies in the community.

The suggested study utilises a pragmatic approach, where all participants with clinical knee OA that would have been eligible for a face-to-face program are included if they can handle a computer, tablet or smartphone.

To summarise, the total study duration, including recruitment and the two assessment visits, will be 12-15 months. The key stages are detailed below;

- Individuals who agree to attend for a clinical assessment will participate for two appointments. This appointment will last approximately 2-3 hours.
- They will be seen at the Academic Rheumatology Unit, Clinical Sciences Building, Nottingham City Hospital and will be asked to come between 8.00am and 10.00am without having had breakfast or any drink other than water.
- Transport (taxi) will be arranged if required and any travel expense will be reimbursed.
- Our Research Nurses will get a 15ml blood sample from the participant and also ask the participant to provide a urine sample.
- Once blood and urine samples have been collected participants will be offered a light breakfast and drink refreshment before a brief assessment to confirm medical history and current medications. Questionnaires such as WOMAC, MSK-HQ and Numeric Rating Scale will be collected.
- Physiological measurements such as 30 seconds sit to stand (30CST), time up and go (TUG) and Muscle strength assessment will be taken at this point.

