**Harm**

No risks are associated with the intervention; however we will record any serious adverse event or harms and will report in publications.

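### Adverse events are collected by participant-initiated reporting with unequal contact between arms, so published harms may be incomplete and not comparable by arm

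*Combined protocol and SAP*

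**What the plan says.** **Protocol, ADVERSE EVENTS.** Two routes are given, both started by the participant. For serious events: "Participants will be asked to contact the study site immediately in the event of any serious adverse event". For any event: "Participants can contact physiotherapists". Once an event is known, the rule is thorough: "Any adverse event will be recorded and closely monitored until resolution, stabilisation or until it has been shown" that the intervention was not the cause. Nothing says that staff will ask.

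**Protocol, Study Regimen.** The web arm receives a personal physiotherapist's contact details through the programme and can reach the physiotherapist by chat or telephone throughout the six weeks. It also gets reminders: "The program encourages the physical activity by sending email prompts on a regular basis". For the other arm, "Control group will continue with their routine self-management which is offered in the community setup", and at the end "They will be re-assessed after six weeks on the primary objective measures". No study contact between visits is described for controls.

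**Protocol, Known Side Effects.** The listed effects are: "Increased knee, hip or low back pain and one reported case of increased hypertension".

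**SAP, Harm.** After stating that the intervention carries no risk, the SAP says "we will record any serious adverse event or harms and will report in publications". The SAP section on confidence intervals and p-values rules out safety analyses on the same ground.

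**The concern.** A harm count depends on how often events occur and on how often they come to notice. Here the second factor rests on participants' initiative, and the opportunity to mention a problem in passing is greater in one arm. Someone in conversation with a physiotherapist about exercises has an easy occasion to mention a sore hip. A control has to decide that the sore hip concerns the study and then make contact.

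Two misreadings are possible. An excess in the web arm could be taken as harm when it partly reflects better detection. A low total could be taken as confirming the SAP's statement that there is no risk, when it partly reflects that nobody asked. Later tabulation cannot repair either, because the weakness lies in collection. The primary pain analysis is not affected.

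**Working it through.** The plan gives no adverse event rate, reporting rate or safety sample size, so there is no figure to reproduce. The check is a trace of the capture routes, followed by an illustration on assumed values.

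**1. Routes by arm**

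| Route | Web arm | Usual care | Where |
|---|---|---|---|
| Contact study site (serious events) | yes | yes | Protocol, ADVERSE EVENTS |
| Contact physiotherapists (any event) | yes | yes, not limited to one arm | Protocol, ADVERSE EVENTS |
| Study contact number | yes | unclear | Protocol, Compliance |
| Programme physiotherapist, chat or telephone for six weeks | yes | none described | Protocol, Study Regimen |
| Email reminders | outgoing only | none described | Protocol, Study Regimen |
| GP as independent source | not told of participation | not told of participation | Protocol, Involvement of Participant's General Practitioner |
| Scheduled adverse-event question | none | none | Protocol, Study Regimen; SAP, Secondary Objectives and Outcome variables |

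The nearest scheduled item is a short check of medical history and medication at the clinic appointment. It is not described as an adverse-event enquiry. Participants may also leave without giving a reason (Protocol, Recruitment), and no section provides a harms enquiry for those who miss week 6.

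**2. What the outcome measures already cover**

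The SAP (Timing of outcome assessments) has all outcomes collected at baseline and six weeks in both arms. Worse knee pain is therefore seen equally in both through NRS and WOMAC. These are analysed as group change scores (SAP, Outcome variables and Analysis methods), not as individual events. Nothing in the plan uses them to count hip or back pain events, new diagnoses or healthcare contacts.

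**3. How unequal detection would act**

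Let n be the number per arm, r the true risk (the same in both arms), and d the probability that an event is recorded.

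- Expected recorded events = n × r × d.
- Ratio of recorded risks = (r × d_web) / (r × d_control) = d_web / d_control.

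Inputs: n = 67 is planned in the documents; r = 0.20 and all values of d are assumptions. True events per arm: 67 × 0.20 = 13.4.

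| d web | d control | Recorded, web | Recorded, control | Ratio | P(Fisher two-sided p < 0.05) |
|---|---|---|---|---|---|
| 0.9 | 0.9 | 12.1 | 12.1 | 1.00 | 0.03 |
| 0.9 | 0.7 | 12.1 | 9.4 | 1.29 | 0.06 |
| 0.9 | 0.5 | 12.1 | 6.7 | 1.80 | 0.19 |
| 0.8 | 0.3 | 10.7 | 4.0 | 2.67 | 0.36 |

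In the third row, 12.06 + 6.70 = 18.76 of 26.8 true events are recorded, or 70%, so the total is also short. The trial stopped with 105 participants completing both visits. At about 52 per arm (an even split is assumed), the third row becomes 52 × 0.20 × 0.9 = 9.4 against 52 × 0.20 × 0.5 = 5.2, with probability 0.14.

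The direction is not fixed either. The documents do not say that what is told to the programme physiotherapist enters the trial's adverse event record. If it did not, and detection were 0.5 in the web arm against 0.9 in controls, the ratio would be 0.5 / 0.9 = 0.56.

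**The case against.** A reader might infer that recorded harms will differ between arms through detection alone, that the web arm has far more reporting channels, and that a false risk ratio near 2 is to be expected. The documents do not support this.

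- Both routes in the protocol's adverse event section are open to all participants, and the contact number under Compliance may be too. Email prompts are outgoing reminders, not reporting channels.
- No detection rate is given. Any ratio, including those tabulated above, restates the detection probabilities put in, and true exercise-related events could differ as well.
- The SAP promises to record and report harms. It promises no counts by arm and excludes safety analyses, so no between-arm harm comparison is planned.
- Both arms have a week-6 visit at which an event could be noted. That capture depends wholly on volunteering is an inference from silence.
- Knee pain, the first-named effect, is measured alike in both arms.

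All of this stands and limits the point to what may happen. It does not remove the point. Access between visits is still unequal, nobody is instructed to ask, and published harms will be read by arm and beside a statement of no risk whether or not a test is planned.

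**Conclusion.** The concern holds in a limited form. Adverse event capture as written is passive in both arms, with additional between-visit contact in the web arm only, so reported harms may be incomplete and differentially ascertained. Neither the size nor the direction can be derived; the recorded ratio equals the ratio of two unknown detection probabilities. The gap concerns mainly hip and back pain, new diagnoses and healthcare contacts, since knee pain is partly covered symmetrically.

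The conclusion rests on reading the visit descriptions and outcome lists as complete. If a case report form outside these documents already carries a standard enquiry, the sponsor need only cite it. There is also an internal contradiction: the SAP says there is no risk (Confidence intervals and p-values; Harm), and its stopping section that no adverse event was expected, while the protocol lists adverse effects under Known Side Effects and ADVERSE EVENTS.

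**What to change.** **For any visit still to be held.** Add to the protocol's ADVERSE EVENTS section and the visit list in Study Regimen: at week 6, once outcome measures are complete, every participant in both arms is asked the same short fixed questions about the preceding six weeks, covering new or worse knee, hip or back pain, any new diagnosis or change of treatment, and any healthcare contact. Asking last protects the blinded examiner's outcome assessments. Put the same questions by telephone to those who do not attend. Record solicited and volunteered events separately, and base any between-arm statement on solicited events only. This equalises the opportunity to report; because participants know their allocation, it does not guarantee equal reporting.

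**For visits completed before the stop on 19 March 2020.** These cannot be repaired. The SAP should state that capture was passive with unequal contact, and draw neither a between-arm nor a no-risk conclusion from the counts.

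**In either case.** Reconcile the SAP's no-risk statements with the adverse effects listed in the protocol.

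Adding blood pressure measurement is optional and not part of this fix.

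**Cost.** A short form, a few minutes per visit and some telephone calls. The reported event count will rise and look less favourable. For completed visits the cost is a few sentences in the SAP and the report.

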## **ETHICAL AND REGULATORY ASPECTS**

### **Involvement of Participant's General Practitioner**

Participant's GPs will not be informed that their patient has agreed to participate in the study.

### **Ethics Committee and Regulatory Approvals**

The study will not be initiated before the protocol, consent forms and participant information sheets have received approval / favourable opinion from the Research Ethics Committee (REC), and the respective National Health Service (NHS) Research & Development (R&D) department. Should a protocol amendment be made, that requires REC approval, the changes in the protocol will not be instituted until the amendment and revised informed consent forms, and participant and GP information sheets (if appropriate) have been reviewed and received approval / favourable opinion from the REC and R&D departments. A protocol amendment intended to eliminate an apparent immediate hazard to participants may be implemented immediately notifying the REC as soon as possible and approval is requested. Minor protocol amendments only for logistical or administrative changes may be implemented immediately, and the REC will be informed.

The study will be conducted in accordance with the ethical principles that have their origin in the Declaration of Helsinki, 1996; the principles of Good Clinical Practice, and the Department of Health Research Governance Framework for Health and Social Care, 2005.

## **Informed Consent and Participant Information**

The process for obtaining participant informed consent will be in accordance with the REC guidance, and Good Clinical Practice (GCP) and any other regulatory requirements that might be introduced. The investigator or their nominee and the participant shall both sign and date the Consent Form before the person can participate in the study.

The participant will receive a copy of the signed, and dated forms and the original will be retained in the Study records.

The decision regarding participation in the study is entirely voluntary. The investigator or their nominee shall emphasize to them that consent regarding study participation may be withdrawn at any time without penalty or affecting the quality or quantity of their future medical care, or loss of benefits to which the participant is otherwise entitled. No study-specific interventions will be done before informed consent has been obtained.

The investigator will inform the participant of any relevant information that becomes available during the course of the study and will discuss with them, whether they wish to continue with the study. If applicable, they will be asked to sign revised consent forms.

If the Consent Form is amended during the study, the investigator shall follow all applicable regulatory requirements pertaining to approval of the amended Consent Form by the REC and use of the amended form (including for ongoing participants).

## **Records**

### **Study Forms**

Each participant will be assigned a study identity code number, and this will be used on the study forms as well as other trial documents and the electronic database. This will be a randomly generated unique participant identifier. An additional identifier will be used to allow validation of participants ID and prevent number being transposed. This additional identifier will consist of participant's initials at the end of unique participant identifier number.

Study forms will be treated as confidential documents and held securely in accordance with regulations. The investigator will make a separate confidential record of the participant's name, date of birth, local hospital number or NHS number, and Participant Study Number, to permit identification of all participants enrolled in the trial, in accordance with regulatory requirements and for follow-up as required.

Study forms shall be restricted to those personnel approved by the Chief or local Principal Investigator and recorded in a Study Personnel Log. All paper forms shall be filled in using a black ballpoint pen. Errors shall be lined out but not obliterated by using correction fluid and the correction inserted, initialled and dated.

The Chief or local Principal Investigator shall sign a declaration ensuring the accuracy of data recorded in the study form.

## **Sample Labelling**

Each participant will be assigned a unique study identification code number for use on the samples, consent forms and other study documents and the electronic database.

### **Source documents**

Source documents shall be filed at the investigator's site and may include but are not limited to, consent forms, study records, field notes, interview transcriptions and audio records. A study form may also completely serve as its own source data.

### **Direct access to source data/documents**

The study form and all source documents, including progress notes and copies of laboratory and medical test results, shall be made available at all times for review by the Chief Investigator, Sponsor's designee and inspection by relevant regulatory authorities.

### **Data Protection**

All trial staff and investigators will endeavour to protect the rights of the trial's participants to privacy and informed consent and will adhere to the Data Protection Act, 1998. The study forms will only collect the minimum required information for the purposes of the trial. Study forms will be held securely, in a locked room, or locked cupboard or cabinet. Access to the information will be limited to the trial staff and investigators and relevant regulatory authorities (see above). The computer held data including the trial database will be held securely and password protected. All data will be stored on a secure dedicated web server. Access will be restricted by user identifiers and passwords (encrypted using a one-way encryption method). Information about the trial in the participant's medical records / hospital notes will be treated confidentially in the same way as all other confidential medical information.

Electronic data will be backed up every 24 hours to both local and remote media in encrypted format

## **QUALITY ASSURANCE & AUDIT**

### **Insurance and Indemnity**

Insurance and indemnity for clinical study participants and study staff are covered within the NHS Indemnity Arrangements for clinical negligence claims in the NHS, issued under cover of HSG (96)48. There are no special compensation arrangements, but study participants may have recourse through the NHS complaints procedures.

The University of Nottingham as research sponsor indemnifies its staff, research participants and research protocols with both public liability insurance and clinical trials insurance. These policies include provision for indemnity in the event of a successful litigious claim for proven non-negligent harm.

### **Study Conduct**

Study conduct will be subject to systems audit for inclusion of essential documents; permissions to conduct the study; CVs of study staff and training received; local document control procedures; consent procedures and recruitment logs; adherence to procedures defined in the protocol (e.g. inclusion / exclusion criteria, random selection of suitable participants for Phase II and Phase III, timeliness of visits); accountability of study materials and equipment calibration logs.

### **Study Data**

Monitoring of study data shall include confirmation of informed consent; source data verification; data storage and data transfer procedures; local quality control checks and

procedures, back-up and disaster recovery of any local databases and validation of data manipulation. This will be managed by the direct study team.

Entries on study forms will be verified by inspection against the source data. A sample of the forms (10%) will be checked on a regular basis for verification of all entries made. In addition, the subsequent capture of the data on the study database will be checked. Where corrections are required these will carry a full audit trail and justification.

Study data and evidence of monitoring and systems audits will be made available for inspection by the REC as required.

